### 7.15 Patient Withdrawal

The Investigator will make every reasonable effort to keep each patient on treatment. However, if the Investigator removes a patient from the trial treatment or if (s)he declines further participation final assessments will be performed, if possible. All the results of the evaluations and observations, together with a description of the reasons for trial withdrawal, must be recorded in the CRF.

In the event of a patient's decision to withdraw from the trial, the Investigator must ascertain from which aspects of the trial the patient wishes to withdraw, and record the details on the appropriate CRF. All patients will continue to be followed-up (if they agree), and all information and tissue samples collected up until the point of retraction, will be retained and analysed.

Patients who are removed from treatment due to adverse events (clinical or laboratory) will be treated and followed up according to accepted medical practice. All pertinent information concerning the outcome of such treatment must be recorded in the CRF.

The following are justifiable reasons for the Investigator to withdraw a patient from trial:

- Withdrawal of consent
- Serious violation of the trial protocol (including persistent patient attendance failure and persistent non-compliance)
- Withdrawal by the Investigator for clinical reasons not related to the trial drug treatment

This section should also be applied in the event of continuation of treatment beyond 10 weeks.

A patient that has not received any IMP treatment will be non-evaluable and therefore will be replaced.

## 8. ADVERSE EVENT REPORTING

The collection and reporting of Adverse Events (AEs) will be in accordance with the Medicines for Human Use Clinical Trials Regulations 2004 and its subsequent amendments. Definitions of different types of AE are listed in Appendix 3. The Investigator should assess the seriousness and causality (relatedness) of all AEs experienced by the patient (this should be documented in the source data) with reference to the *current IB Investigator Brochure*.

### 8.1 Reporting Requirements

#### 8.1.1 Adverse Events

All medical occurrences which meet the definition of an AE (see Appendix 4 for definition) should be reported. Please note this includes abnormal laboratory findings including those that are not clinically significant.

##### 8.1.1.1 Pre-existing conditions

Any pre-existing conditions should be reported as medical history, and should not be reported as an AE unless the condition worsens by at least one CTCAE grade during the trial. The condition, however, must be reported in the CRF.

#### 8.1.2 Serious Adverse Events

Investigators should report AEs that meet the definition of an SAE (see Appendix 3 for definition)

##### 8.1.2.1 Monitoring pregnancies for potential Serious Adverse Events

It is important to monitor the outcome of pregnancies of patients in order to provide SAE data on congenital anomalies or birth defects.

In the event that a patient or their partner becomes pregnant during the SAE reporting period please complete a Pregnancy Notification Form (providing the patient's details) and return to the ALS Trials Office as soon as possible. If it is the patient who is pregnant provide outcome data on a follow-up Pregnancy Notification Form. Where the patient's partner is pregnant consent must first be obtained and the patient should be given a Pregnancy Release of Information Form to give to their partner. If the partner is happy to provide information on the outcome of their pregnancy they should sign the Pregnancy Release of Information Form. Once consent has been obtained provide details of the outcome of the pregnancy on a follow-up Pregnancy Notification Form. If appropriate also complete an SAE Form as detailed below.

### 8.1.2.2 Liver Related Toxicity: Biochemistry

All liver related toxicity: (Biochemistry blood tests) will be reported in accordance with Appendix 5 of the study protocol. Specific information will be provided on a Serious Adverse Event Case Report Form and liver toxicity Case Report Form as applicable. Reporting of these events will need to be via expedited Serious Adverse Event procedures detailed in Section 8.2.1.2 of the protocol. The information relating to these procedures which will be reported under medically significant events (SAE categorisation) is also summarised below.

Other Medically significant events that need to be reported as an SAE include:

- Is associated with liver injury and impaired liver function defined as:
  - o ALT > 3xULN and total bilirubin# > 2xULN (>35% direct), or ALT > 3xULN and INR >1.5.

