# Serum bilirubin fractionation should be performed if testing is available; if unavailable, measure urinary bilirubin via dipstick. If fractionation is unavailable and ALT > 3xULN and total bilirubin > 2xULN, then the event is still to be reported as an SAE. If INR measurement is obtained, the value is to be recorded on the SAE form.

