#### 8.2.1.2 Serious Adverse Events

For more detailed instructions on SAE reporting refer to the SAE Form Completion Guidelines contained in the Investigator Site File (ISF).

AEs defined as serious and which require reporting as an SAE should be reported on an SAE Form. When completing the form, the Investigator will be asked to define the causality and the severity of the AE which should be documented using the CTCAE version 4.0.

On becoming aware that a patient has experienced an SAE, the Investigator (or delegate) must complete, date and sign an SAE Form. The form should be scanned to the Trials Office email address listed below as soon as possible and no later than 24 hours after first becoming aware of the event:

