| 
 
Report the event to Trials Office within 72 hours
 
Complete the liver event CRF and complete an SAE - if the event also meets the criteria for an SAE
 
Perform liver event follow up assessments
 
Monitor the subject until liver chemistries resolve, stabilize, or return to within baseline (see MONITORING below). "Baseline" refers to the laboratory assessments performed closest and prior to dosing of study treatment.
 
 
MONITORING:
 
For bilirubin or INR criteria:
 
 
Repeat liver chemistries (include ALT, AST, alkaline phosphatase, bilirubin) and perform liver event follow up assessments within 24 hrs
 
 | 
 
Viral hepatitis serology
 
Blood sample for pharmacokinetic (PK) analysis, obtained within 7 after an identified liver event if within 6 months post dose.
 
Serum creatine phosphokinase (CPK) and lactate dehydrogenase (LDH).
 
Fractionate bilirubin, if total bilirubin 2xULN
 
Obtain complete blood count with differential to assess eosinophilia
 

 
Record the appearance or worsening of clinical symptoms of liver injury, or hypersensitivity, on the AE report form
 
 |

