|-----------------------------------------------------------------------------------------------------------------------------------------------------------------------------------------------------------------------------------------------------------------------------------------------------------------------------------------------------------------------------------------------------------------------------------------------------------------------------------------------------------------------------------------------------------------------|--------------------------------------------------------------------------------------------------------------------------------------------------------------------------------------------------------------------------------------------------------------------------------------------------------------------------------------------------------------------------------------------------------------------------------------------------------------------------------------------------------------------------------------------------------------------------------------------------------------------------------------------------------------------------------------------------------------------------------------------------------------------------------------------------------------------------------------------------------------------------------------------------------------------------------------------------------------------------------|

1. Serum bilirubin fractionation should be performed if testing is available. If serum bilirubin fractionation is not immediately available, discontinue study treatment for that subject if ALT 3xULN and bilirubin 2xULN. Additionally, if serum bilirubin fractionation testing is unavailable, **record presence of detectable urinary bilirubin on dipstick**, indicating direct bilirubin elevations and suggesting liver injury.
2. All events of ALT  $\geq$  3xULN and bilirubin  $\geq$  2xULN (>35% direct bilirubin) or ALT  $\geq$  3xULN and INR>1.5, if INR measured which may indicate severe liver injury (possible 'Hy's Law'), **must be reported as an SAE (excluding studies of hepatic impairment or cirrhosis)**; INR measurement is not required and the threshold value stated will not apply to subjects receiving anticoagulants

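### Section 8.1.2.2 and Appendix 5 set inconsistent rules for which liver events are SAEs and how fast they are reported, so classification and notification can depend on the section a site followed

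*Protocol*

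**What the plan says.** **Section 8.1.2.2.** The scope is wide: "All liver related toxicity: (Biochemistry blood tests) will be reported in accordance with Appendix 5 of the study protocol". The forms are qualified: "Specific information will be provided on a Serious Adverse Event Case Report Form and liver toxicity Case Report Form as applicable". The route is then given as "Reporting of these events will need to be via expedited Serious Adverse Event procedures detailed in Section 8.2.1.2 of the protocol". Section 8.2.1.2 sets the limit for that route: "as soon as possible and no later than 24 hours after first becoming aware of the event". Section 8.1.2.2 next lists the liver combinations that are SAEs: ALT >3xULN with total bilirubin >2xULN (>35% direct), or ALT >3xULN with INR >1.5. A note covers missing fractionation: "If fractionation is unavailable and ALT > 3xULN and total bilirubin > 2xULN, then the event is still to be reported as an SAE".

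**Appendix 5.** For any liver event the first action is "Report the event to Trials Office within 72 hours". The site completes a liver event form, and an SAE form only where SAE criteria are also met. Footnote 2 makes SAEs of ALT ≥3xULN with bilirubin ≥2xULN (>35% direct), and of ALT ≥3xULN with INR >1.5. The bilirubin row of the same appendix uses ALT >3xULN. Footnote 1 deals with unavailable fractionation by a treatment-discontinuation instruction and a urine dipstick record. It does not give SAE status.

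**Table 3 (Section 9.1)** also gives 72 hours, for the additional-information form on liver toxicity.

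**The concern.** Section 8.1.2.2 cannot be followed literally in both its parts. Reporting under Appendix 5 allows 72 hours and a conditional SAE form; reporting under Section 8.2.1.2 means 24 hours on an SAE form. Section 7.3.1.1 sends sites straight to Appendix 5, so a site that starts there does not meet the 24-hour wording.

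SAE status matters in four places:

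- the primary safety outcome counts SAEs (Sections 2.3 and 12.2.1.1);
- an SAE is one of two ways to satisfy criterion 1 of an intolerable adverse event (Section 2.3), so it can settle the tolerability class of a related grade 3 to 5 event that caused no drug discontinuation longer than three weeks;
- the DMC reviews all SAEs (Section 8.2.5), and a liver event left off an SAE form is outside that review;
- a related SAE stops the patient (Section 7.1.6), and one in a sentinel patient suspends the trial (Synopsis, Trial Stopping Rules).

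**Working it through.** The protocol gives no figure to reproduce: Section 12.6 states that there was no sample size calculation, and no liver event rate is given. The check is to put the rules side by side and classify example results.

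**Deadline.** 24 hours under 8.1.2.2 with 8.2.1.2, against 72 hours under Appendix 5. The gap is 72 − 24 = 48 hours, a ratio of 72/24 = 3. The 72-hour action applies to any liver event, so on its face it includes the bilirubin and INR events that both sections treat as SAEs.

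**Classification.** The results below are hypothetical, in multiples of ULN. Where the bilirubin row of Appendix 5 shows no inequality sign, it is read as at least 2xULN.

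| Result | SAE on the 8.1.2.2 list and note | SAE under Appendix 5 footnote 2 | Liver event in the Appendix 5 rows |
|---|---|---|---|
| ALT 5x or 8x alone | no | no | yes |
| ALT 3.5x for 4 weeks | no | no | yes |
| ALT 3.5x with symptoms | no | no | yes |
| ALT exactly 3x, bilirubin 2.5x, 50% direct | no | yes | no |
| ALT 4x, bilirubin exactly 2x, 50% direct | no | yes | yes |
| ALT exactly 3x, INR 1.6 | no | yes | yes |
| ALT 4x, bilirubin 2.5x, not fractionated | yes | not covered | unclear: the row also asks for >35% direct |
| ALT 4x, bilirubin 2.5x, 50% direct | yes | yes | yes |
| ALT 4x, INR 1.6 | yes | yes | yes |

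Four things follow.

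1. The first three rows are on neither SAE list. The literal routing sentence in 8.1.2.2 nevertheless sends them through the 24-hour SAE procedures; Appendix 5 treats them as 72-hour liver events unless some other SAE criterion is met.
2. Rows four to six differ only because a value sits exactly on a threshold. Row four also shows Appendix 5 disagreeing with itself: an SAE under footnote 2, yet outside its own bilirubin row.
3. The unfractionated case is an SAE under 8.1.2.2 and is not addressed by footnote 2, which requires >35% direct.
4. Away from those cases the two lists agree (last two rows).

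**Scale.** The recruitment target is 15, so one reclassified patient changes SAE incidence by 1/15 = 6.7 percentage points. Recruitment was ended early; if fewer than 15 were treated, each patient counts for more. This is the weight of one patient, not an expected change.

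**The case against.** The best defence reads the passages together. If every liver event were an SAE, the separate list in 8.1.2.2 would serve no purpose. The qualification as to which forms apply, and the reference to Appendix 5, allow this scheme: SAE-level events on the SAE form in 24 hours, other liver events on the liver form in 72. Table 3's 72 hours belongs to a different form. This reading is reasonable and probably intended, but the routing sentence does not say it, and the 72-hour action in Appendix 5 has no exception for SAE-level events.

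The defence is stronger against four further inferences that a reader might draw.

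- *That every liver event enters the primary SAE count under 8.1.2.2.* Reporting route is not classification. Section 8.1.2 ties SAEs to Appendix 3, and under Section 8.2.2 a Clinical Coordinator determines seriousness independently. That step acts only on SAE forms received, so it limits over-counting but does not catch an event that never reached an SAE form.
- *That the anticoagulant wording is a material difference.* Footnote 2 adds: "INR measurement is not required and the threshold value stated will not apply to subjects receiving anticoagulants". Section 8.1.2.2 has no such waiver. But anticoagulant users are excluded (Section 4.1, exclusion 14), and needing one stops ILB (Section 7.1.6). In practice that leaves a patient who starts one after the last dose, within the 30-day SAE window of Section 8.1.3.
- *That the unfractionated case is common.* Section 7.3.1 asks for direct and indirect bilirubin when the total is ≥30, with no units or ULN. Assuming µmol/L, a ULN of 15 or 20 puts 2xULN at 30 or 40, so every total above 2xULN should be fractionated; a ULN of 10 puts it at 20 and leaves totals between 20 and 30 uncovered. Both sections nonetheless provide for fractionation being unavailable.
- *That the sentinel rule can still be triggered or missed.* It needs an SAE related to IMP, and Section 11 places the last treatment visits in March 2020.

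Inequality signs that are simply absent in Appendix 5 may have been lost in extraction, and nothing here rests on them.

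**Conclusion.** The inconsistency is real and stands in the current operative text. It has three parts: the 24-hour and 72-hour instructions overlap for SAE-level liver events; the SAE thresholds differ at exact boundary values, including within Appendix 5; and only 8.1.2.2 gives SAE status when bilirubin is not fractionated. A liver event could therefore be classified or notified differently according to the section followed.

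The size is modest. The number of affected patients is unknown and probably small. The deadline conflict affects when the Trials Office and the DMC hear of an event, not the count. With the last doses in March 2020 and SAE reporting ending 30 days after the last dose, the deadline, patient-stopping and sentinel effects are essentially historical. What remains live is the SAE and tolerability classification in the final report.

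A reader might conclude that the primary SAE table should be derived from laboratory values. The documents do not support that: Appendix 3 leaves medical significance to the investigator.

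A related conflict needs settling at the same time. Section 7.3.1.1 says there are no liver-specific stopping criteria as such, while Appendix 5 footnote 1 contains a discontinuation instruction. This review does not say which is right.

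**What to change.** 1. Reconcile 8.1.2.2, Appendix 5 and Table 3 into one list of liver events that are SAEs, with one set of inequalities and one rule for unavailable fractionation.
2. State one deadline for SAE-level liver events, and state the deadline for the liver form separately.
3. Reconcile Section 7.3.1.1 with Appendix 5 footnote 1.
4. For the final report, check the recorded ALT, bilirubin and INR values against the reconciled list and query any SAE-level event not reported as one. Present this as a supporting listing; the primary count keeps the seriousness assessment of the investigator and the Clinical Coordinator.

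The cost is a text reconciliation of a few passages and one listing from laboratory results that the protocol already has sites record electronically. No new data are needed.

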# Serum bilirubin fractionation should be performed if testing is available; if unavailable, measure urinary bilirubin via dipstick. If fractionation is unavailable and ALT > 3xULN and total bilirubin > 2xULN, then the event is still to be reported as an SAE. If INR measurement is obtained, the value is to be recorded on the SAE form.

### 8.1.3 Reporting period

Details of all AEs will be documented and reported from the signing of the informed consent and will include the collection of all baseline AEs. AE collection will continue until 30 days after the end of treatment visit.

Details of SAEs will be documented and reported for each patient from the date of consent until 30 days after their last administration of trial treatment.

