| Time schedule
Days +/- 1 day                                | Visit 1
Day ≤ 14                                                                                                                                | Visit 2
Day 1   | Visit 3
Day 8 | Visit 4
Day 15 | Visit 5
Day 22 | Visit 6
Day 29 | Visit 7
Day 36 | Visit 8
Day 43 | Visit 9
Day 50 | Visit 10
Day 57 | Visit 11
Day 64 | Visit
13
Day
78                                                                                        | Visit
14
Day
106 | Visit
15
Day
134 | Visit
16
Day
162 |
| 1. Medical history*                                            | X                                                                                                                                                  |                    |                  |                   |                   |                   |                   |                   |                   |                    |                    |                                                                                                                 |                           |                           |                           |
| 2. Eligibility
Assessment                                   | X                                                                                                                                                  | X                  |                  |                   |                   |                   |                   |                   |                   |                    |                    |                                                                                                                 |                           |                           |                           |
| 3. ALSFRS-R                                        | X                                                                                                                                                  | X                  | X                | X                 | X                 | X                 | X                 | X                 | X                 | X                  | X                  | X                                                                                                               | X                         | X                         | X                         |

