## Schedule of Events

\*to include an assessment of any mental or physical contraindications to study entry

\*\* For patients that discontinue treatment prior to Week 10, follow-up should continue 4 weekly, after the end of treatment visit, up to week 24. These visits should all follow the week 16 assessments apart from the final visit which follows week 24.

\*\*\* If patients do not continue treatment after week 10, follow the Follow-up (Observational Period) schedule in Schedule of Assessments (1) Main Trial. If the criteria is met for IMP treatment to continue beyond week 10, follow Schedule of Assessments (2): Treatment Extension after week 10.

\*\*\*\* End of treatment visit should occur 2 weeks after last dose of IMP (as per the Week 12 assessments) regardless of how many treatment doses a patient has received.

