#### 7.1.6 Patient Stopping Rules

Patients will have treatment of ILB stopped if any of the following prospective criteria are met during the treatment period:

- The patient experiences a Serious Adverse Event related to IMP
- If there is a decrease in ALSFRS-R score (>50%) compared to baseline
- If a patient becomes pregnant during the study treatment period
- Unacceptable toxicity – any adverse event which, in the investigators opinion, requires termination of the study drug
- Unforeseen events – any event which in the judgement of the Investigator makes further treatment inadvisable
- SAE requiring discontinuation of treatment
- If a patient requires an anticoagulant e.g Warfarin, Aspirin, Clopidogrel, any novel anticoagulants (NOAC)s or low molecular weight subcutaneous heparin during the clinical trial
- PTT or aPTT > 1.5 x ULN
- INR > 1.8 x ULN

Patients, who stop weekly dosing, will be invited to remain in the observational part of the study up to 24 weeks, to enable assessment of safety related measures. Patients that discontinue ILB and subsequently start or re-commence Riluzole therapy will also be invited to remain in the observational part of the study up to 24 weeks.

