##### (2 weeks after last dose of IMP)

- ALSFRS-R
- Concomitant drug history
- Vital signs (blood pressure, heart rate, body temperature, pulse oximetry and respiration rate). Results of oximetry should be the average of three recordings. Body weight and Body Mass Index (BMI)
- ECG
- Lung Function Tests (FVC)
- SNIP
- Haematology tests (FBC, ESR)
- Coagulation tests (to include INR, APTT and PT)
- Biochemistry tests (Troponin I, C-reactive protein (CRP), Glucose, Calcium)
- Creatinine Kinase
- Urea & Electrolytes (U&Es), Liver Function Tests (LFTs)
- Thyroid Function Tests (TSH, Free T4)
- Immunoglobulins (IgG, IgM)
- Quality of Life questionnaire (ALSAQ-40)
- Urinary p75ECD
- NfL levels
- Collection of exploratory biomarker blood samples
- Pregnancy test for WOCBP
- Adverse Event assessment/reporting

An end of treatment visit must be performed 2 weeks from the last dose of ILB regardless of how many treatment doses a patient has received.

In the event a patient discontinues treatment prior to the end of week 10 the follow up schedule as detailed in the Schedule of Assessments 1 should be followed using the Week 16 schedule as a guide for visits. If drug administration ends at week 10, follow up visits should continue every 4 weeks from week 12 at which point patients should continue with the follow up schedule as per the Schedule of Assessments 1 table. i.e. week 12, week 16, week 20 and week 24 follow up visits.

If drug administration is approved to continue after week 10 but the patient discontinues early, prior to the end of week 24, follow up visits should continue every 4 weeks until week 24 where an end of treatment visit will occur.

Follow up schedule for patients who finish treatment at week 10

#### Week 16

##### Visit 13

- ALSFRS-R
- Concomitant drug history
- Vital signs (blood pressure, heart rate, body temperature, pulse oximetry and respiration rate). Results of oximetry should be the average of three recordings. Body weight
- Haematology tests (FBC, ESR)
- Coagulation tests (to include INR, APTT and PT)
- Biochemistry tests (Troponin I, C-reactive protein (CRP), Glucose, Calcium)
- Urea & Electrolytes (U&Es), Liver Function Tests (LFTs)
- Quality of Life Questionnaire (ALSAQ-40)
- Adverse Event assessment/reporting

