**Week 24****Visit 15**

- ALSFRS-R
- Concomitant drug history
- Vital signs (blood pressure, heart rate, body temperature, pulse oximetry and respiration rate). Results of oximetry should be the average of three recordings. Body weight and Body Mass Index (BMI)
- ECG
- Lung Function Tests (FVC)
- SNIP
- Haematology tests (FBC, ESR)
- Coagulation tests (to include INR, APTT and PT)
- Biochemistry tests (Troponin I, C-reactive protein (CRP), Glucose, Calcium)
- Creatinine Kinase
- Urea & Electrolytes (U&Es), Liver Function Tests (LFTs)
- Thyroid Function Tests (TSH, Free T4)
- Immunoglobulins (IgG, IgM)
- Quality of Life questionnaire (ALSAQ-40)
- Urinary p75ECD
- NfL levels
- Collection of exploratory biomarker blood samples
- Pregnancy test for WOCBP
- Adverse Event assessment/reporting

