#### 12.2.1 Analysis of Primary Outcome Measures

##### 12.2.1.1 Safety

The number of SAEs and AEs will be calculated and summarised. Furthermore, the number of patients experiencing each will be calculated. Each of these analyses will be broken down by grade, relatedness, event type (admitting event for SAEs); expectedness (SAEs only) and sequelae (SAEs only).

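### Section 8.1.3 closes SAE collection 14 days before AE collection, and on the main schedule both end-points contradict the safety visits planned to Week 24

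*Protocol*

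**What the plan says.** Protocol section 8.1.3 sets two reporting periods, both opening at consent. For adverse events, "AE collection will continue until 30 days after the end of treatment visit". Serious adverse events are documented and "reported for each patient from the date of consent until 30 days after their last administration of trial treatment". The anchors differ: a visit in one case, a dose in the other.

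The footnotes to the schedule of assessments link them: "End of treatment visit should occur 2 weeks after last dose of IMP", however many doses were given. Section 7.14 repeats this, then says of patients who stop early in the extension that "follow up visits should continue every 4 weeks until week 24 where an end of treatment visit will occur".

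Other places ask for safety data over a longer period. Section 7.1.6 says that anyone who comes off ILB "will be invited to remain in the observational part of the study up to 24 weeks, to enable assessment of safety related measures". The main schedule marks adverse event reporting as running throughout the follow-up columns to Week 24. Section 7.14 lists "Adverse Event assessment/reporting" at the Week 16, Week 20 and Week 24 visits.

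The incidence of SAEs and AEs is a primary outcome (section 2.3), with no period stated. Section 12.2.1.1 says only: "The number of SAEs and AEs will be calculated and summarised".

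**The concern.** An SAE is an AE that meets a seriousness criterion, so one would expect serious events to be collected for at least as long as non-serious ones. Section 8.1.3 does the reverse. The two primary safety counts then refer to different periods in the same patient.

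Sites also hold two incompatible instructions for late follow-up: section 8.1.3 closes the windows, while the schedule and section 7.14 ask for adverse event assessment at later visits. Two patients with the same late event could be counted differently, depending on which text their site followed.

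Other things depend on the SAE window. Tolerability needs a related grade 3 to 5 event linked either to an SAE or to a drug discontinuation of more than three weeks; once planned dosing is complete, in general only the SAE route remains. The central causality and expectedness assessment (8.2.2) starts from SAE forms, committee review covers SAEs (8.2.5), and pregnancy notification is tied to the SAE reporting period (8.1.2.1).

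**Working it through.** The protocol gives no figure for the length of either window, so there is none to reproduce. The check is day arithmetic on its own visit days, assuming uninterrupted weekly dosing.

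**Inputs**
- Dose in week w falls on Day 1 + 7(w − 1). The Week 10 column of the main schedule is headed "Visit 11 Day 64".
- End-of-treatment (EOT) visit = last dose + 14 days; Day 78 (± 3 days) after a Week 10 last dose (7.14).
- SAE window end = last dose + 30. AE window end = EOT + 30 (8.1.3).
- Follow-up visits at Weeks 16, 20 and 24: Days 106, 134 and 162.

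**Last dose at Week 10 (Day 64)**
- SAE end: 64 + 30 = Day 94.
- AE end: 64 + 14 + 30 = Day 108.
- Gap: 108 − 94 = 14 days, so Days 95 to 108 are in the AE window only. With the EOT visit on Days 75 to 81, the AE end is Day 105 to 111 and the gap 11 to 17 days.
- Week 16 (Day 106): 12 days after the SAE end and 2 days before the nominal AE end, so outside the SAE window only.
- Week 20 (Day 134): 40 days after the SAE end, 26 after the AE end.
- Week 24 (Day 162): 68 days after the SAE end, 54 after the AE end.

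**Earlier stop, for example Week 5 (Day 29)**
- SAE end: 29 + 30 = Day 59. AE end: 29 + 14 + 30 = Day 73. Both come well before Week 24, to which four-weekly follow-up is meant to run.

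**Extension patients, EOT at last dose + 14**
- Last dose Week 13 (Day 85): AE end 85 + 44 = Day 129, before Week 20. From Week 14 (Day 92) it is Day 136, so Week 20 is covered for AEs.
- Last dose Week 17 (Day 113): AE end Day 157, before Week 24. From Week 18 (Day 120) it is Day 164, so Week 24 is covered for AEs.
- Last dose Week 24 (Day 162): SAE end Day 192, AE end Day 206. The conflict with the Week 20 and Week 24 visits does not arise; the 14-day gap does.

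**Extension patient stopping at Week 12 (Day 78), two readings of section 7.14**
- SAE end on either reading: 78 + 30 = Day 108.
- EOT two weeks after the last dose: AE end 78 + 14 + 30 = Day 122, gap 14 days.
- EOT at Week 24: AE end 162 + 30 = Day 192, gap 84 days.

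**The case against.** The strongest reply is that late events may well be captured despite section 8.1.3. The schedule and section 7.14 call for adverse event assessment through Week 24. Section 8.2.1.1 has AEs completed at each visit, with an SAE form where applicable; section 8.2.1.2 requires an SAE form once the investigator becomes aware of a serious event; and the death form carries no time limit. This stands against any claim that events were lost. It does not remove the contradiction, because section 8.1.3 is the section that defines the reporting period and it says otherwise.

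A second reply is that 30 days after dosing is not evidently short for a drug with a half-life of about 3 hours that is said to be eliminated in under 24 hours (1.1.5, 1.2.3). Patients are only invited to stay under observation, and some may start riluzole, so late events will mix disease progression and other treatment into an uncontrolled count. This is fair. The point here is not that 30 days is wrong, but that two anchors are used and neither fits the protocol's own schedule. The mixing is a reason to report late events separately.

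A third reply is that the analysis plan can define the analysis period. It can restrict collected data to a common period, but it cannot add events that a site, following section 8.1.3, did not report.

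Finally, treatment visits ended in March 2020, so a new window cannot act prospectively. That is correct and shapes the remedy. The remote visit in 2021 lists ALSFRS-R, ALSAQ-40 and medication but not adverse events, so as specified it will not close the gap.

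**Conclusion.** The concern holds as an internal inconsistency over the observation period of a primary outcome. The 14-day difference between the SAE and AE end-points follows directly from the text whenever the EOT visit is two weeks after the last dose. The conflict with both the Week 20 and Week 24 visits holds for every patient whose last dose is at or before Week 10, and on that EOT definition for extension patients up to a Week 13 last dose (Week 20) or a Week 17 last dose (Week 24). It does not hold for those dosed to the end of the extension. The two EOT dates move the AE end-point by 70 days (192 − 122) for a last dose on Day 78.

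Three stronger readings are tempting and not supported:
- *Late serious events are under-counted.* This follows only if section 8.1.3 prevailed over the schedule and section 7.14 in practice. The documents do not say which prevailed, and they give no event rates from which to size a shortfall.
- *The share of follow-up days outside each window measures the error.* That would require every day to Week 24 to count as ILB safety time, which the protocol does not establish.
- *Events before the first dose are counted as ILB safety data.* Section 8.1.3 calls them baseline events, the AE form records start date and causality, and separating treatment-emergent events is a matter commonly left to the analysis plan.

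**What to change.** - In section 8.1.3, keep collection from consent and state one common end-point for AEs and SAEs that agrees with the scheduled safety visits. One example is the later of the Week 24 visit and EOT + 30 days: Day 162 for a Week 10 last dose, Day 206 for a Week 24 last dose.
- Settle a single definition of the EOT visit. Until then, that example still gives Day 162 or Day 192 for a last dose on Day 78.
- Reconcile section 8.1.3, the adverse event row and EOT footnote of the schedule, and the Week 16, 20 and 24 lists in section 7.14, so that all give the same period.
- Because treatment has ended, retrieve serious events in the uncovered interval from the hospital notes.
- Report events after the last dose, including any after starting riluzole, separately from on-treatment events.

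The cost is a short amendment, a review of notes for at most 15 patients, and a field marking each event as on or after treatment. The downside is that a few more late events may be listed, some due to ALS progression or riluzole rather than ILB; separate reporting keeps them from obscuring the on-treatment picture.
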